### Data collection & statistical analyses

To measure mean percent weight change, we will use EHR weights, which are collected similarly across UC health center visits, and DPP session weights for UC beneficiaries who enroll in DPP. Baseline covariate differences between those with and without attrition will be examined and we will then adjust for any covariates found to be significantly different (*p* < 0.05) between attrition groups in order to satisfy the Missing at Random assumptions of the mixed effects models. Because attrition could be a consequence of our primary outcome (i.e. weight) our missing data may be Missing Not at Random. In this instance we will utilize pattern mixture modeling to impute missing valuies. We will conduct within-subject analysis estimates of UC DPP Initiative effectiveness among those who received a “full intervention dose” (i.e., Group 1 prediabetes awareness letters and enrolled in DPP). For this primary analysis, we will use a mixed effects linear regression model to compare percent weight change within Group 1 subjects 12 and 24 months before DPP enrollment (pre period) and 12 and 24 months after enrollment (post period). Models for the trajectory of percent weight change will be specified with a random intercept for person with nested random slope for time from enrollment measured on a continuum. Average within-person between time-period (post vs. pre-enrollment) differences in the trajectory for % weight change will be modeled using a fixed effect interaction term of time-by-time-period to test for between time-period differences in the rate of % weight change. These models will be fit using a random intercept for person and random slope for time-period (post vs pre). A fixed effect of time-period will be used to estimate the average between time-period difference in % weight change adjusting for the corresponding length of time over which the change was observed. For both models, exploratory post-hoc analyses will also consider additional subject level covariates (age, gender, race, ethnicity, number of co-morbidities, number of DPP sessions attended, education level and years employed at the institution), as well as DPP site. Interactions of the difference over time (rates or mean levels) by these subject characteristics or site will also be explored to evaluate whether there is a differential benefit of the program for certain groups of beneficiaries (i.e., heterogeneity in treatment effect) and across sites. In the presence of statistically significant (*p* < 0.05) interactions, the models will be stratified so as to allow for potential heterogeneity in the covariates as well.

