### Sample size and power calculations

For our primary outcome of % weight change at 12-month follow-up within subjects, we will use 5% weight change to estimate power based on the 2002 DPP randomized controlled trial [4] as well as National DPP recognition standards [22]. With a proposed sample size of *N* = 50 using a two-sided alpha level of 0.05, we would demonstrate 80% power to detect a paired difference of at least 3.3% and have > 98% power to detect our target weight change of 5%. For our outcome of weight change at 12-month follow-up between subjects, we conservatively assume that the average % weight loss for those in Group 2 (prediabetes notified) and Group 3 (usual care) will be 2 and 0% respectively. These values will yield about a 3% difference in weight loss between our comparison groups. Using an independent samples t-test as a simplification of the mixed effects analysis plan with a two-sided alpha of 0.05, we will have 90% power to detect our assumed between group difference of 3% with the proposed sample sizes of 50 (Group 1; 10 per site) and 500 (Group 2; 100 per site). Using the same assumptions, the proposed sample sizes of *N* = 550 Group A + B and *N* = 500 Group 3 would yield 99% power to detect the assumed 3% difference in the percentage weight change between the groups. We would additionally have 80% power to minimally detect a between group difference of 2.5 and 1.1% with these sample sizes. All sample sizes account for an anticipated 20% loss to follow-up [7]. We will not be powered to detect differences in rates of incident type 2 diabetes, but we will examine trends over time using validated EHR and claims data algorithms [23, 24]. Metformin is not specifically highlighted in the UC DPP Initiative, but since some beneficiaries with prediabetes may also seek out this option, [4, 25] we will also examine rates of metformin uptake using prescription data available in the EHR.

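### Covariates meant to make missing at random plausible are chosen by a p<0.05 dropout comparison, which cannot serve that purpose, and the status of the pattern-mixture analysis is unclear

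*Protocol article*

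**What the plan says.** The section on data collection and statistical analyses of the protocol article sets out the handling of attrition in three steps.

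- Baseline covariates are compared between people with and without attrition, and "we will then adjust for any covariates found to be significantly different". The threshold is explicit: "significantly different (*p* < 0.05) between attrition groups".
- The stated purpose is "in order to satisfy the Missing at Random assumptions of the mixed effects models".
- The article then grants that dropout could be a consequence of weight itself, so that data may be missing not at random, and continues: "In this instance we will utilize pattern mixture modeling to impute missing valuies".

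The primary analysis in the same section is a within-person comparison of the periods before and after enrolment in Group 1. Age, gender, race, ethnicity, co-morbidities, site and similar variables enter only in exploratory post-hoc models. No covariate is named for inclusion regardless of the screen. The section does not say whether the screen is run within Group 1, within each group, or over all groups together.

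**The concern.** Missing at random is a statement about conditioning: given what is in the model, dropout must be unrelated to the unobserved weights. A covariate is needed if it relates both to dropout and to those weights, given the weights already observed. Whether its difference between dropouts and completers reaches p<0.05 depends largely on how many people drop out. In a small group a real predictor is easily missed. In a large one a trivial difference is easily admitted. Either way the model is settled by the data and not by subject-matter reasoning.

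The primary estimate comes from the smallest group. If the screen is applied there, the adjustment meant to protect that estimate is likely to be incomplete. The analysis that answers the article's own worry, that weight drives dropout, is introduced in words that can be read as a commitment or as a condition. If it is a condition, nobody can verify from the data that it has been met.

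**Working it through.** **Inputs.** From the section on sample size and power calculations: "With a proposed sample size of *N* = 50 using a two-sided alpha level of 0.05" for the primary comparison; "50 (Group 1; 10 per site) and 500 (Group 2; 100 per site" for the between-group comparison; 500 in Group 3; 20% anticipated loss in all sample sizes. The screening threshold is p<0.05, taken here as two-sided. The documents give no covariate distributions, so differences of 0.3, 0.5 and 0.8 SD are assumed as a range.

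**The plan's own figure.** The article states 80% power for a paired difference of 3.3% and more than 98% for 5%. It gives no SD. Solving the noncentral t for 3.3% at 80% power with n = 50 gives an SD of 8.16, and that SD gives 98.9% power for 5%, so the statement is reproduced. With n = 40 the implied SD is 7.26 and the power for 5% is again 98.9%. The figures therefore do not show whether 50 is the number before or after loss, and both cases are carried forward.

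**Size of the comparison.**

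- 50 enrolled: 0.20 × 50 = 10 lost, 40 retained.
- 50 evaluable: 50 / 0.80 = 62.5, so 63 enrolled and 13 lost.
- Pooled over 50 + 500 + 500 = 1,050: 210 lost, 840 retained. Of the 210, 10 come from Group 1 and 200 from Groups 2 and 3.

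**Power of the screen.** For a two-sample t-test on a standardised difference d, the noncentrality is λ = d / √(1/n₁ + 1/n₂) with n₁ + n₂ − 2 degrees of freedom. For 10 vs 40, √(0.100 + 0.025) = 0.354. At d = 0.5, λ = 1.41 against a critical value of 2.01, which gives 28% power. For 13 vs 50 the divisor is 0.311, and for 210 vs 840 it is 0.077.

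| Comparison | 0.3 SD | 0.5 SD | 0.8 SD | Difference detected with 80% power |
|---|---|---|---|---|
| 10 vs 40 | 13% | 28% | 60% | 1.01 SD |
| 13 vs 50 | 16% | 35% | 72% | 0.89 SD |
| 210 vs 840 | 97% | >99% | >99% | 0.22 SD |

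A binary covariate present in 50% of dropouts and 30% of completers would be flagged at 10 vs 40 with 23% power (normal approximation) or 17% (Fisher's exact test).

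Run within Group 1, the screen misses a 0.5 SD predictor of dropout about 65-72% of the time.

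**Ceiling on the bias, by assumption.** If those lost did 3 to 5 percentage points worse (an assumption; the documents give no figure), a completers-only mean would be off by 0.20 × 3 = 0.6 to 0.20 × 5 = 1.0 points, against a 5% target. The planned mixed model also uses the weights observed before dropout, so this is an upper bound for a cruder analysis and not the effect of the screening rule.

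**The case against.** Four replies carry weight.

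1. *The text does not place the screen in Group 1.* True. The comparison is described before Group 1 is mentioned, and pooled over all groups it has ample power. A reader might infer that the screen certainly compares 10 with 40, or that the adjustment set will differ by group; the article supports neither. But a pooled screen draws about 200 of its 210 dropouts from people who never enrolled in the program, so it says little about who leaves Group 1.

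2. *Low power is not no power.* Also true. A 0.8 SD difference would be found 60-72% of the time. A reader might go further and conclude that the rule will usually adjust for nothing. That does not follow. With eight independent covariates (an assumption), each differing by 0.3 SD, the chance that at least one is flagged at 10 vs 40 is 1 − 0.868⁸ = 68%; at 0.5 SD it is 1 − 0.717⁸ = 93%. Even if none differs it is 1 − 0.95⁸ = 34%. The fault is an incomplete and noisy set, not necessarily an empty one.

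3. *The mixed model conditions on observed weights.* It does, through EHR and session weights. An omitted covariate biases the result only if it still relates to the unobserved weights given those. This limits the harm but does not justify the rule.

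4. *Pattern-mixture modelling is already promised.* On one reading it is: the article says data may be missing not at random and then commits to the method. So it cannot be claimed that the analysis will be skipped. The wording equally allows a conditional reading, and that ambiguity stands.

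That an article condenses the full plan is no answer on the main point, because the selection rule is stated and not merely omitted.

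**Conclusion.** The point holds in a limited form. The article fixes a selection rule that cannot do what it is said to do. Within Group 1 the rule would probably omit moderate predictors of dropout; pooled, it would mainly describe attrition in other groups. These results assume 20% loss, a two-sided test, equal variances, and covariate differences of 0.3 to 0.8 SD. How far the primary estimate would move cannot be derived from the documents; the 0.6-1.0 point figure is only an assumption-based ceiling for a completers-only analysis. The design is not undermined, but the rule and the status of the pattern-mixture analysis should be settled before the data are analysed.

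**What to change.** - **Drop the significance screen.** Attrition comparisons can still be reported descriptively, stating the groups in which they are made.
- **Prespecify a short covariate set on subject-matter grounds,** for example age, sex, baseline BMI and co-morbidity count. Enter each with its interaction with time or period, because a time-constant main effect alone largely leaves a within-person contrast unchanged. Leave out weight change before baseline: the primary model compares the periods before and after enrolment, so that change is part of the outcome.
- **State that the pattern-mixture analysis is run unconditionally** as a sensitivity analysis, over a stated range of assumed worse outcomes in those lost, up to return to baseline weight.
- **Label any bias figure** as an assumption-based upper bound.

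The cost is wording, one more reported analysis, and a few parameters in Group 1: four main effects and four interactions with period in the example. A longer list would be hard to carry. Adding five campuses (four parameters) and race/ethnicity (three, assuming four categories) makes 4 + 4 + 3 = 11 main effects, or 22 with interactions, for about 40 completers.

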**Methods:**

The goal of our study is to conduct a multifaceted evaluation of the UC DPP Initiative using the Reach, Effectiveness, Adoption, Implementation, and Maintenance (RE-AIM) framework. Our evaluation will integrate unique and diverse UC data sources, including electronic health record (EHR) data, administrative claims, campus-based DPP cohort data, qualitative interviews and site visits. Our primary outcome of interest is the mean percent weight change among three groups of overweight/obese UC beneficiaries at risk for diabetes at 12-month follow-up. Secondary outcomes include mean percent weight change at 24-month follow-up, barriers and facilitators associated with implementatio, as well as  the degree of program adoption and maintenance.

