### Aim 1: effectiveness of UC DPP

To assess the effectiveness of the UC DPP Initiative, we will examine mean percent weight change from baseline at 12 month follow-up and 24 month follow-up within and between three groups of overweight/obese UC beneficiaries. Group 1 includes overweight/obese beneficiaries with documented prediabetes who receive UC DPP Initiative prediabetes awareness letters and enroll in DPP (i.e., receive “full treatment”). Group 2 includes overweight/obese beneficiaries with documented prediabetes who receive UC DPP Initiative prediabetes awareness letters, but do not enroll in DPP. Group 3 includes overweight/obese UC beneficiaries without documented prediabetes who are not included in the UC DPP Initiative (do not receive prediabetes awareness letters and do not enroll in DPP). Group 3 serves as a control group to account for secular trends and/or concurrent programs that may affect weight change outcomes among UC beneficiaries (such as weight management services any overweight/obese UC beneficiaries may receive as part of routine care). The primary outcome will be % weight change at 12-month follow-up within those who received a “full intervention dose” (i.e., Group 1) and secondary outcomes will compare mean % weight change between UC beneficiaries (Groups 1 vs. 2 and Group 1 + 2 vs. Group 3).

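### The primary outcome and its power concern percent weight change at 12 months, but the only term the plan says it will test is a pre/post difference in rate, with no stated 12-month limit on the fit

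*Protocol article*

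**What the plan says.** Aim 1 sets the outcome: "we will examine mean percent weight change from baseline at 12 month follow-up and 24 month follow-up". It then names the primary: "The primary outcome will be % weight change at 12-month follow-up within those who received a “full intervention dose” (i.e., Group 1"). The abstract places the later time point second: "Secondary outcomes include mean percent weight change at 24-month follow-up". The sample size section powers the within-subject 12-month change as a paired difference. With N = 50 and two-sided alpha 0.05 it gives 80% power at 3.3% and more than 98% at 5%.

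The section on data collection and statistical analyses, under the label of the primary analysis, describes a mixed-model comparison: "compare percent weight change within Group 1 subjects 12 and 24 months before DPP enrollment (pre period) and 12 and 24 months after enrollment (post", where the last bracket labels the later window. The trajectory model has a "random intercept for person with nested random slope for time from enrollment measured on a continuum". Two quantities follow:

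- A slope difference, "modeled using a fixed effect interaction term of time-by-time-period to test for between time-period differences in the rate of % weight change".
- A level difference: "A fixed effect of time-period will be used to estimate the average between time-period difference in % weight change". Its allowance for elapsed time is worded as "adjusting for the corresponding length of time over which the change was observed".

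The section states no contrast or predicted value at month 12, does not limit the primary fit to 12 months, and does not say which quantity decides the primary question.

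**The concern.** The outcome and the power calculation refer to how far weight has moved by month 12. The one term said to be tested refers to how fast weight moves over the fitted period. The two agree if loss is linear over that period. If weight falls early and then levels off or is partly regained, a slope over a longer span understates the 12-month change and can even change sign. A programme that reached its 5% target at 12 months could then show almost nothing on the tested term. The stated power would not describe that test either, because it was computed for a paired difference.

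**Working it through.** **1. The plan's own power figure.** Inputs from the sample size section: N = 50, two-sided alpha 0.05, 80% power at 3.3%. No SD is given, so it is solved from that statement.

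- Normal approximation: SD = 3.3 × √50 / (1.960 + 0.842) = 8.33. Power at 5% = Φ(5 × √50 / 8.33 − 1.960) = Φ(2.285) = 98.9%.
- Noncentral t: SD = 8.16, power at 5% = 98.9%. With 40 completers after 20% loss, SD = 7.26 and power is again 98.9%.

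The stated figure of more than 98% is reproduced, as the power of a paired 12-month difference.

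**2. What the slope returns when loss is not linear.** The document gives no trajectory, so this one is an assumption: pre-period flat at 0%; after enrolment linear to -5% at month 6, -5% at month 12, linear to -3% at month 24; one weight per month. The true post-minus-pre contrast at month 12 is -5%. Slope = Σ(t − t̄)y / Σ(t − t̄)².

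- Months 0-24: Σy = -94.5, Σty = -1206.5, t̄ = 12. Numerator = -1206.5 + 12 × 94.5 = -72.5; denominator = 1300. Slope × 12 = -0.67%.
- Months 1-24 (enrolment weight counted as pre-period): t̄ = 12.5. Numerator = -1206.5 + 12.5 × 94.5 = -25.25; denominator = 1150. Slope × 12 = -0.26%. With a flat pre-period this is the pre/post interaction.
- Months 0-12: Σy = -47.5, Σty = -360.83, t̄ = 6. Numerator = -360.83 + 6 × 47.5 = -75.83; denominator = 182. Slope × 12 = -5.00%.

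The exact agreement in the last line comes from the bend falling midway. Moving it, still over months 0-12, gives:

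| Month at which -5% is reached | Slope × 12 |
|---|---|
| 3 | -3.5% |
| 5 | -4.6% |
| 6 | -5.0% |
| 7 | -5.3% |

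**3. The period difference, read as an average level.** With the enrolment weight in the pre-period, the 24-month mean difference is -94.5 / 24 = -3.9%. Adding signed time from enrolment as a covariate gives -3.7%. Over months 0-12 the post-period mean is -47.5 / 13 = -3.7%.

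**4. Sensitivity.** The change was varied from -2.5% to -6% at month 6 and from -7% to 0% at month 24, with -5% at month 12 throughout. Over 0-24 months with monthly weights, slope × 12 ran from -3.5% to +1.2% and the period average from -5.1% to -2.4%. Timing of weights also matters. On the base path, slope × 12 is -0.7% with monthly weights, -1.5% with weights at 0, 12 and 24 months only, and -2.0% with half-monthly weights in year one and then months 18 and 24.

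**The case against.** The strongest reply is that the text allows readings under which the mismatch shrinks.

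- *Separate fits.* The reference to 12 and 24 months may mean two analyses, one per horizon. The abstract ranks the horizons as primary and secondary, and Group 3's baseline is defined by two alternative look-back windows, which points the same way. The 24-month figures would then not bear on the primary outcome. This stands as a plausible reading, but the primary-analysis text does not say it, and a 12-month slope is still not the 12-month change unless the shape is favourable.
- *Change scores.* The second model adjusts for the time over which each change was observed. That suggests each person contributes one pre-period change and one post-period change. At the 12-month horizon this would be the paired difference that was powered. This also stands, so a reader who infers that neither model can deliver the primary outcome goes further than the text supports.
- *Multiplicity.* A reader might infer two primary tests at 0.05 and a false-positive rate of 1 − 0.95² = 9.8%. The document does not support this. It speaks of testing for the slope and of estimating for the period term, attaches no 0.05 threshold to either there, and takes both from the same persons and weights, so independence fails.
- *Front-loading.* A reader might assume dense early session weights and sparse later record weights. The article names the two sources of weights and 16 core sessions but gives no timing, so this can only be an assumption.
- *Detail left to an analysis plan.* Windows and splines may well be. But the article does name the primary model and its tested term, and what it names is a rate. Continuous time does not exclude curvature, although a single rate per period implies a line.

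**Conclusion.** The point holds in limited form. The outcome and power are stated for the 12-month change, while the one term stated to be tested is a difference in rate. The fit is not confined to 12 months and no decisive quantity is named. On the assumed path the tested quantity, scaled to 12 months, is -0.7% (or -0.3%) over 24 months and -3.5% to -5.3% over 12 months, against a true -5%. The size therefore depends on horizon, shape and timing of weights, none of which the article settles. The trajectories are illustrative assumptions and do not predict the trial's result. The conclusion does not say that the planned models must miss the primary outcome, because the second model may recover it if it compares 12-month change scores.

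**What to change.** State that the single primary test is the model-based post-minus-pre contrast in percent weight change at month 12 within Group 1. Either of two routes would serve:

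- Keep the mixed model but let time be flexible, as visit windows or as a spline with a change-point at enrolment.
- Limit the primary fit to the 12-month horizon and compare 12-month change scores, saying so explicitly.

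Report month 24 as the same contrast, labelled secondary, and the slope and period average as descriptive. Outcome, test and power calculation would then refer to one quantity, with the stated 80% at 3.3% and more than 98% at 5% applying as a paired-difference approximation. The same data are used. The cost is wording, a few more fixed-effect parameters on the flexible-time route, and a slightly wider interval at month 12.

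### The rate model tests a pre-to-post change in slope but names no random effect for that change, so its standard error is too small if people differ in how much their slope changes; by how much cannot be fixed from the article.

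*Protocol article*

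**What the plan says.** All of this stands in the protocol article under *Data collection & statistical analyses*, within the text introduced as the primary analysis of Group 1.

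- **Comparison.** % weight change within person, "12 and 24 months before DPP enrollment (pre period) and 12 and 24 months after enrollment (post period").
- **Random effects, first statement.** Trajectory models have a "random intercept for person with nested random slope for time from enrollment measured on a continuum".
- **Rate test.** A "fixed effect interaction term of time-by-time-period to test for between time-period differences in the rate of % weight change".
- **Random effects, second statement.** Straight after the rate test: "These models will be fit using a random intercept for person and random slope for time-period (post vs pre").
- **Mean-level test.** "A fixed effect of time-period will be used to estimate the average between time-period difference in % weight change", adjusted for the length of time observed. The text then speaks of two models, one for rates and one for mean levels.
- **Data.** "we will use EHR weights, which are collected similarly across UC health center visits, and DPP session weights for UC beneficiaries who enroll in DPP". The number of weights per person is not given.

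The next paragraph carries the same models into the group comparisons by adding an interaction with group. *Sample size and power calculations* treats the 12-month outcome as a paired difference with N = 50.

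**The concern.** The rate test asks whether the average person's slope changes at enrollment. Its standard error must reflect how much that change differs from person to person.

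A random slope for time gives each person one slope that holds before and after enrollment. A random slope for period gives each person a shift in level. With either, every person is assumed to have the same change in slope. Any real variation in that change is pushed into the residual or into the other random effects, and repeated weights on the same 50 people then count as nearly independent evidence about it. Intervals become too narrow, and an average change of zero is declared significant too often. The distortion grows with the number of weights per person.

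Variation between people is to be expected in a lifestyle program, and the article itself plans to look for heterogeneity in treatment effect.

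**Working it through.** **1. Reproduce the stated power.** The article gives N = 50, two-sided alpha 0.05, 80% power for a paired difference of 3.3% and more than 98% for 5%. It gives no SD, so solve for it.

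- Normal formula: SD = 3.3 × √50 / (1.960 + 0.842) = 8.33. Noncentral t: SD = 8.16.
- Power at 5% with that SD: 98.9%, which agrees with the article.
- With 40 people (after 20% loss) the SD is 7.45 (normal) or 7.26 (t), and power at 5% is again 98.9%.
- The between-group figure (80% power for 2.5% with 50 vs 500) gives an SD of about 6.0 for a single change. From 8.16² = 2 × 6.0² × (1 − ρ), the pre/post correlation is ρ = 1 − 66.6/72 = 0.08.

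**2. What the paired SD implies.** Assume that 8.16 is the SD of D = (W₁₂ − W₀) − (W₀ − W₋₁₂), the post-enrollment 12-month change minus the pre-enrollment one. Measurement noise with SD σ contributes (1 + 4 + 1)σ² = 6σ². The rest is the person-to-person SD of the rate change, √(8.16² − 6σ²):

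- σ = 1: 7.8; σ = 2: 6.5; σ = 3: 3.5.
- For no variation at all, σ would have to be 8.16/√6 = 3.3% of body weight, or 8.16/2 = 4.1% if the two changes share no weight.

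**3. Simulate the rate test with no average change.** Settings: 50 people; 12 months each side; REML; fixed time, period and time × period; Wald test of the interaction; 500 runs per row. Assumed: intercept SD 3, common slope SD 3 per year, period-shift SD 2. (The period shift was not subtracted in step 2. Taking off its variance of 4 would lower the three SDs only to 7.5, 6.2 and 2.9.) Entries are type I error, with the ratio of model SE to true SE in parentheses.

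| Weights pre + post | σ | Random time | Random period | Person-level slope-difference test |
|---|---|---|---|---|
| 2 + 2 | 1 | 11% (0.82) | 1% (1.19) | 3% |
| 2 + 2 | 2 | 9% (0.85) | 3% (1.09) | 5% |
| 2 + 2 | 3 | 6% (0.97) | 3% (1.10) | 5% |
| 3 + 3 | 1 | 29% (0.55) | 16% (0.77) | 7% |
| 3 + 3 | 2 | 14% (0.75) | 7% (0.92) | 5% |
| 3 + 3 | 3 | 9% (0.88) | 6% (0.95) | 6% |
| 5 + 5 | 1 | 44% (0.42) | 28% (0.57) | 5% |
| 5 + 5 | 2 | 22% (0.62) | 16% (0.73) | 5% |
| 5 + 5 | 3 | 8% (0.88) | 7% (0.93) | 6% |
| 3 + 16 | 1 | 45% (0.38) | 24% (0.61) | 5% |
| 3 + 16 | 2 | 24% (0.58) | 15% (0.74) | 3% |
| 3 + 16 | 3 | 10% (0.88) | 8% (0.95) | 6% |

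Monte Carlo error is about 1 percentage point near 5% (√(0.05 × 0.95/500)) and about 2 near 45%. Fitting the time and period slopes together is no cure: type I error reaches 51% with 3 + 16 weights and σ = 1.

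**4. Cross-check.** If the SE is r times its true value, type I error is about 2Φ(−1.96r). For r = 0.55 this gives 28% (simulated 29%), for 0.38 it gives 46% (45%), and for 0.88 it gives 8.5% (8-10%).

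**5. A middle case.** With 4 + 4 weights, σ = 1, SD of a 12-month change 6 and ρ = 0.08, a run of 540 data sets gave 34% with a random time slope (mean SE 0.59 against a true 1.21), 23% with a random period slope and 5.4% with separate random pre and post slopes. A separate run of 150 gave 35%, 24% and 7%.

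**The case against.** **The numbers are assumed.** This stands. The article gives no residual SD, no count of weights and no SD of rate change. A reader might infer that the standard error is simply half its proper size, or that type I error is 23-34%. Those figures describe one scenario. With little variation in rate change the test is near nominal.

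**The named time points favor a mild result.** The article names 12 and 24 months on each side. With two weights per period the range is only 6-11% (time slope) or 1-3% (period slope). This stands in part. Time is modeled on a continuum and session weights are added after enrollment, so more weights per person are likely.

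**The rate test may not decide the primary outcome.** This also stands. Aim 1 defines the primary outcome as % weight change at 12 months, and it is powered as a paired difference. A reader might infer that the primary result as a whole is invalid. The documents do not support that: in the mean-level model the random period effect matches the fixed effect tested.

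**The wording may already mean the right thing.** The word nested could mean slopes nested within person and period, which would be the cure. The text does not say so, and its next statement names a random slope for period alone.

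**Exact random effects are usually left to a full plan.** That would answer silence. Here the article states the structures, and as stated they do not match the test.

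**Conclusion.** The concern holds for the rate test. The article names its random effects, and none lets the tested change in slope vary between people. If that change varies, the standard error is too small and type I error exceeds 5% once there are more than a few weights per person. The paired SD of about 8.2% implied by the article's own power statement makes such variation likely, if it is read as the SD of the difference between 12-month changes.

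The size is not known. Under residual SDs of 1-3% and 2 to 16 weights per period, type I error lies between about 1% and 45% for the two stated structures, and the time-slope reading is the worse one.

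The group comparisons inherit the structure wherever they compare rates; that extension was not simulated. The mean-level period model is not affected. A reader might also infer a loss of power from clustering by campus or DPP cohort. The article gives no intraclass correlation and no cohort size for Group 1, so no figure can be attached to it, and it is not part of this conclusion.

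**What to change.** - **Rate model.** Specify separate random pre- and post-enrollment slopes per person (equivalently, add a random time-by-period term), or test each person's difference between post and pre 12-month change directly. Use the same structure where group comparisons concern rates.
- **Fallback.** Name in advance a person-level test or a cluster-robust standard error by person, in case the model does not converge.
- **Mean-level model.** Keep the random period effect, and state that it belongs to this model.
- **Inputs.** State which weights enter, roughly how many are expected per person and period, and the SD behind the power figures.

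Cost: no new data. Intervals for the rate change will be wider but correctly sized. With about 50 people and few pre-enrollment weights the fuller model may not converge, which is why the fallback should be fixed beforehand.
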